## Abstract

**Background:**

In malaria-endemic areas, residents of modern houses have less malaria than those living in traditional houses. This study will determine if modern housing provides incremental protection against clinical malaria over the current best practice of long-lasting insecticidal nets (LLINs) and prompt treatment in The Gambia, determine the incremental cost-effectiveness of the interventions, and analyze the housing market in The Gambia.

**Methods/design:**

A two-armed, household, cluster-randomized, controlled study will be conducted to assess whether improved housing and LLINs combine to provide better protection against clinical malaria in children than LLINs alone in The Gambia. The unit of randomization will be the household, defined as a house and its occupants. A total of 800 households will be enrolled and will receive LLINs, and 400 will receive improved housing before clinical follow-up. One child aged 6 months to 13 years will be enrolled from each household and followed for clinical malaria using active case detection to estimate malaria incidence for two malaria transmission seasons. Episodes of clinical malaria will be the primary endpoint. Study children will be surveyed at the end of each transmission season to estimate the prevalence of *Plasmodium falciparum* infection, parasite density, and the prevalence of anemia. Exposure to malaria parasites will be assessed using light traps, followed by detection of *Anopheles gambiae* species and sporozoite infection. Ancillary economic and social science studies will undertake a cost-effectiveness analysis and use qualitative and participatory methods to explore the acceptability of the housing modifications and to design strategies for scaling-up housing interventions.

**Discussion:**

The study is the first of its kind to measure the efficacy of housing on reducing clinical malaria, assess the incremental cost-effectiveness of improved housing, and identify mechanisms for scaling up housing interventions. Trial findings will help inform policy makers on improved housing for malaria control in sub-Saharan Africa.

**Trial registration:**

ISRCTN Registry, ISRCTN02622179. Registered on 23 September 2014.

**Electronic supplementary material:**

The online version of this article (doi:10.1186/s13063-016-1400-7) contains supplementary material, which is available to authorized users.

## Background

There have been considerable gains made in malaria control in sub-Saharan Africa, with malaria prevalence dropping by half, and the incidence of clinical disease falling by 40 % from 2000 to 2015 [1]. Yet the disease remains a substantial public health problem, with 188 million cases and 395,000 malaria deaths in 2015 [2]. The reduction in malaria has been achieved largely by the massive scaling up of vector control, with long-lasting insecticidal nets (LLIN) and indoor residual spraying (IRS). However, the future success of these interventions is threatened by the growing problem of insecticide-resistant mosquitoes [3], some of which are resistant to all four classes of insecticide currently available for use in public health [4]. Thus, an urgent need exists to develop supplementary interventions that are not reliant on insecticides. This objective is also advocated by Roll Back Malaria (RBM) and the United Nations Development Program (UNDP, which has stated the need for “making actions outside the health sector essential elements of malaria control” [5]. The need for “good” housing to reduce malaria is echoed throughout this RBM/UNDP document. Recently, the RBM Board [6], noting that continued progress in the fight against malaria is central to the attainment of the Sustainable Development Goals, has committed to implementing the aim through development of a work plan that reaches beyond the traditional health sector to include “environment, climate change, housing, sanitation, agriculture, education, and other sectors invested in the fight against poverty.” Thus, a growing enthusiasm exists for using housing as an intervention against malaria, as illustrated further by the new RBM workstream on malaria and housing (http://archiverbm.rollbackmalaria.org/mechanisms/vcwgWorkstream9.html).

Is housing protective? Improved housing was thought to have contributed to the elimination of malaria in the USA [7, 8] and to its decline in Europe [9]. Narrative reviews suggested that “good housing” is protective in many tropical countries [10, 11]. More recently, a systematic review and meta-analysis of the literature on housing and malaria provided stronger evidence that “good housing” is protective against malaria [12]. Residents of modern homes had 42 % lower odds of malaria infection compared to traditional homes and a 54–65 % lower incidence of clinical malaria. Yet the overall evidence indicates low quality, and only one randomized controlled trial has been conducted of house screening to date. This trial showed that the use of simple untreated screens on the doors and windows and closing the eaves in typical rural African houses reduced the prevalence of anemia in children by 50 % [13]. Nonetheless, the impact of “good” housing on clinical episodes of malaria, the benchmark measurement for assessing malaria interventions, has not been quantified.

The hypothesis supporting housing as being protective against malaria in sub-Saharan Africa is based on the observation that 79–100 % of malaria transmission occurs indoors at night [14]; so preventing the entry of malaria mosquitoes indoors [10, 13] should dramatically reduce malaria risk. Traditional thatched-roofed houses nearly always have open eaves, with a gap between the top of the wall and the roof, through which *Anopheles gambiae*, the principal African malaria vector, enters the house. Metal-roofed houses more frequently have closed eaves, so installing metal-roofs and closing the eaves should reduce the entry of malaria vectors. Because screening the doors and windows also reduces mosquito house entry [13], we hypothesize that a combination of metal roofs, closed eaves, and the installation of screening on the doors and windows should measurably reduce clinical malaria. In addition, to encourage air circulation and help cool the room, while also preventing the entry of mosquitoes into the intervention houses, we propose to install screened windows and doors. Although we consider the interventions safe, the possibility exists that the reduced indoor airflow may increase respiratory disease in children living in screened houses. For this reason, we will also measure respiratory illness in our study cohort.

The long-term effectiveness and potential impact of housing as a malaria intervention will depend on its cost-effectiveness, acceptability to householders, and the feasibility of implementation at scale. Therefore, alongside the trial, we will undertake a cost-effectiveness analysis and use qualitative and participatory methods to explore the acceptability of the housing modifications and to design strategies for scaling up housing interventions. The incremental costs and benefits associated with house improvements, as well as the demand and supply of construction material and skill, are invaluable data to inform policymakers in their decision to adopt the interventions as policy. However, very limited evidence exists on the cost-effectiveness of improved housing on health, and the little information available is focused on interventions implemented in high-income countries [15]. Analysis of the housing sector in sub-Saharan Africa is growing, but most of the studies are concentrated in a few countries and in urban areas [16].

We view improved housing not as a stand-alone-intervention but as one that should be incorporated with established and effective vector-control interventions such as LLINs. Thus, our goal is to determine whether there is any additional benefit in improving rural homes over the current best practice of using LLINs alone for protecting children against clinical malaria, to determine the incremental cost-effectiveness of the interventions, and analyze the housing market in The Gambia.

### Study objectives

#### Clinical

##### Primary objective

The primary clinical objective its to assess whether improved housing (metal roof, closed eaves, improved ventilation, and screened doors and windows) and LLINs provide added protection against clinical malaria in children with the LLINs alone over two malaria transmission seasons of follow-up.

### Secondary objectives

The secondary clinical objectives include the following:To determine whether improved housing reduces the rate of parasite infection, parasite density, and anemia in childrenTo assess whether improved housing is associated with a rise in respiratory infections

#### Entomological

##### Primary objective

The primary entomological objective is to assess whether improved housing and LLINs reduce vector density inside houses when compared with the LLINs alone.

#### Economic and social science

##### Primary objective

The primary economic and social science objective is to assess the incremental costs, benefits, and cost-effectiveness of these interventions.

### Secondary objective

The secondary economic and social science objectives are as follows:To explore the acceptability of the house modifications to the residentsTo analyze the housing market in The Gambia for the identification of economic barriers to scale-up

## Methods/design

### Study area and participant eligibility

The study is situated in the far east of The Gambia, in the Upper River Region (URR), an area of open Sudan savanna. The climate consists of a single rainy season from May to October followed by a long dry season. This defines the highly seasonal malaria transmission, with most malaria episodes experienced during or immediately following the rainy season. This region covers an area of 1995 km^2^ and is bisected by the river into the north and south banks. The population of the region was 182,586 in 2003, the most recent census, with most living in small discrete rural villages in houses made with mud or cement walls and thatched or metal roofs. The study’s field station is based at Basse Santa Su town (UTM coordinates 13.3167 N, -14.2167 W), which is the only sizeable urban area in the region.

Rural villages located on the north and south bank of the Gambia River will be selected. We will discuss the study with village leaders, including women in each potential study village, and proceed if given approval. Community sensitization will be followed by a survey to identify suitable houses.

A total of 800 traditional thatched-roofed houses constructed with mud walls, open eaves, and without ceilings or screening, with two children aged 6 months to 13 years, will be selected. Consent will be sought from the house owners (and residents) for them to join the study by field assistants (Additional file 1).

Once all houses in the intervention arm have been modified, we will seek consent from the parents/carers for a resident child to join the study cohort from both arms of the study (using supplementary materials). After explaining the purpose of the study to the household heads, only children whose parents have given written, informed consent for their child to be included in the study will be enrolled (Additional file 2). The purpose of the study and requirements of the study according to the capability and assent sought will be explained to eligible children > 12 years old.

Each arm of the study will contain 400 houses, and one resident child will be enrolled from each house. The child will be selected randomly from those aged 6 months to 13 years, except if they expect to be away during several month of the transmission season. No distinctions will be made regarding gender or ethnic group. As much as possible, we will encourage the residents of the study houses not to move house during the study.

### Design

The study design is summarized in Fig. 1 and is a two-armed household-clustered randomized controlled study using a generalized, randomized, complete, block design, with the village as the block. At least two control and two intervention houses will be used from each village, but interventions will not be introduced in > 10 % of houses in each village to reduce the chance that mosquitoes prevented from entering an intervention house will enter a control house in greater numbers than normal. Previous studies in The Gambia suggest that this risk is low and that mosquito diversion is unlikely to increase exposure in unprotected homes [17, 18]. A total of 400 houses will be included in each arm of the study, and one resident child will be enrolled from each house. If the resident child enrolled in the study leaves the house for whatever reason, they will be replaced by another child from the same house. The clinical study will take place over 2 years, with clinical follow-up and entomological studies being conducted over two consecutive transmission seasons (June to December); at the end of this period, households in the control group will be provided with a metal roof and screening if they desire it. Children will be enrolled at the start of the first transmission season and will be followed for clinical malaria using active case detection (ACD) to estimate malaria incidence for two malaria transmission seasons. These children will also be surveyed at the beginning and end of each transmission season to estimate the prevalence of *Plasmodium falciparum* infection, parasite density, and the prevalence of anemia. Exposure to malaria parasites will be assessed using light traps in 60 houses in each arm of the study, followed by detection of *An. gambiae* species and sporozoite infection.

**Fig. 1 Fig1:**
[figure not shown]
Schematic representation of the trial

Ancillary economic and social science studies will undertake a cost-effectiveness analysis and use qualitative and participatory methods to explore the acceptability of the housing modifications and to design strategies for scaling-up housing interventions. The schedule of enrolment, interventions and assessment is shown in Additional file 3.

### Randomization

Since there is considerable variation in malaria risk between villages [19], houses will be randomized to the study arms by MP, stratified by village using a computer subroutine in a blinded manner so that an equal number of houses are selected in each arm of the study in each village at baseline. Every effort will be made to ensure that the arms of the study are balanced by number and village. Furthermore, if a house leaves the study in year 1, efforts will be made to replace it in year 2. Once the intervention is in place, one child will be selected randomly and recruited from each house. The PI and trial statistician are responsible for the house and child identification, as well as the enrollment and intervention assignment.

A total of 120 houses will be selected for monthly light trap collections of mosquitoes from the 800 houses enrolled, stratified by intervention, village, and geography so that an equal number of houses are selected in each arm of the study in each village, and the subsample is equally spread over the study area.

Stratified randomization by village will reduce the likelihood of chance imbalances between study arms. In addition, data on potential confounding factors including number of people in the house, burning incense [20] will be collected and corrected for use in the analysis. The interventions will be closely monitored for quality and durability and to document any bias among the villages.

### Interventions

Enrolled houses will all have thatched roofs and mud walls in good condition, and the occupants, provided with a sufficient number of LLINs (Olyset, Sumitomo Chemical) to cover all sleeping places. At the time of donation, we will follow national guidelines to encourage their correct use, as this is the current best practice. In the intervention arm, represented by modern housing, we propose to modify existing rectangular-plan and circular-plan thatched roof houses, so they will have metal roofs, closed eaves [19], and screening on the doors and windows (Fig. 2, *n* = 400).The control arm, representing traditional houses, will be left with thatched roofs and open eaves (*n* = 400) until the end of the study. A metal-louvered screened door will be installed in the front of the house, and a wooden-screened door, at the back [21]. Households will be enrolled, and the interventions put in place from February 2015 to June 2016. Homeowners will be encouraged to keep their doors closed at night.

**Fig. 2 Fig2:**
[figure not shown]
Prototype rectangular-plan (**a**) and circular-plan thatched-roof houses (**b**)

### Clinical data collection and patient treatments

The baseline clinical survey of all study children will take place in May/June 2016 and will determine malaria infection, splenomegaly, and anemia. Clinical follow-up will start in June 2016, and cover both rainy seasons (June to December 2016 and 2017). Incidence of clinical malaria will be determined by ACD during twice weekly house visits from June to November each year [20]. Clinical respiratory disease will be determined at the same time. Clinical surveys of all study children will be repeated at the end of each rainy season (November/December) and during June 2017. Surveys to measure damage to the interventions and the integrity of the control houses will be carried out annually. Surveys to measure LLIN use by all study house residents will be made in July and October each year. The final clinical survey of the child cohort will take place in December 2017.

No treatment will be administered by the study personnel. However, any patient diagnosed with malaria or suspected to have pneumonia or other illnesses will be referred to the local health system for treatment according to the Gambian National Guidelines.

### Clinical evaluations

The main morbidity outcome will be the incidence of clinical disease assessed by ACD; data from this will provide the primary endpoint of the study. The axillary temperature will be taken twice weekly and if ≥ 37.5 °C, a rapid diagnostic test (Paracheck Pf, Orchid Biomedical Systems, Goa, India) for malaria will be made, and the breathing rate will be checked. The presence of a cough and either a raised age-specific respiratory rate or chest indrawing will also be assessed in children deemed to be unwell by the parent or guardian. Serious adverse events (SAE) will be recorded during both transmission seasons. Sick children will receive referral notes to the nearest health post/facility, and treatment will be documented at the next biweekly visit.

During the cross-sectional surveys, clinical surveys will be done of all study children, who will be examined for general health and the presence of an enlarged spleen. A finger prick sample will be taken to measure the blood hemoglobin immediately using a spectrophotometer (HemoCue, Ängelholm, Sweden) and to prepare thick smears for later detection and quantification of *Plasmodium* parasites. Blood films will be stained in the field by project staff, transported to the laboratory, and read independently by two microscopists blinded to the identity of the child. Any discrepancy will be resolved by a third senior microscopist. Children with sickness or disease will be referred for treatment.

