### Safety considerations

No potential pharmacological intervention or treatment by project staff is proposed in this study. However, the possibility remains that our modified housing may increase the risk of acute respiratory infections. We will therefore assess the study children for respiratory disease at each study visit, i.e., twice weekly during the transmission season. Since respiratory infections are common in children in this area [25], we selected this age group as the most sensitive indicator group. Adverse events, whether attributed or not to improved housing, will be collected. If a participant develops a SAE during the course of the study, this will be reported by the field staff to the study clinician within 2 days of the start of the SAE. A SAE is defined as any adverse event that results in death, is life threatening, requires hospitalization or prolongation of existing hospitalization, or results in disability/incapacity. The study clinician will record and manage the SAE in accordance with the MRC Unit standard procedures (SOP-CTS-009 for “Recording, Management and Reporting of Adverse Events”). The study clinician will report the SAEs to the Chief Investigator, who will report these regularly to the Data Safety and Monitoring Committee and Study Steering Committee (SSC; see supplementary material for roles and responsibilities). All SAEs will be followed up until resolution.

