### Study endpoints

#### Clinical

The primary clinical endpoint will be the incidence of clinical malaria, which is determined by active case detection (ACD) and defined as a body (axillary) temperature of ≥ 37.5 °C, together with the presence of *P. falciparum* parasites detected by microscopy.

The secondary clinical endpoints will be (1) *P. falciparum* parasite rates, (2) prevalence of splenomegaly, (3) prevalence of anemia, and (4) an incidence of respiratory infection, measured as a cough and either a raised age-specific respiratory rate or chest indrawing.

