### Sample size rationale

#### Clinical

The combination of closed eaves and screening on the door reduces house entry of malaria mosquitoes by 65 % [26], and we anticipate a similar proportional reduction in malaria incidence in the proposed study but consider that a reduction of at least 35 % would not only be of public health importance but also good value for the money. We simulated incidence data allowing for within-house correlation between the years, based on incidence data collected using passive case detection from the proposed study area in 2010 (0.0468 and 0.0442 malaria episodes per child month at risk, CMAR) and 2011 (0.0321 and 0.0341 CMAR). The number of cases were inflated twofold, as we will use active case detection (ACD). Correlated event data were generated from a bivariate Poisson distribution to give random simulated correlated counts for each house over the two years. Each village was assumed to contain an equal number of houses in the control and intervention arm. Fifty sets of 1,000 data points were simulated for each of the two to ten houses in the 40 to 100 villages. The significance of the difference in incidence rate between the control and the intervention arms was quantified using a generalized estimating equation (allowing for the within-house correlation) with a log link for each of the data sets and house and village parameters. The proportion of each set of 1,000 simulations with a significant *p* value of less than 5 % for the difference between the control and the intervention arm was the estimated power. This shows that when following one child per house for 2 years, five houses in 80 villages are required in each study arm (black circle, i.e., 400/arm) to detect a 35 % reduction in malaria cases with more than 80 % power at the 5 % significance level (Fig. 3).

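### The article gives two rules for who is checked for respiratory disease; the conditional one ties the only named harm endpoint to fever and unblinded parental report, so detection could differ by arm

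*Protocol article*

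**What the plan says.** Background raises the worry that "the reduced indoor airflow may increase respiratory disease in children living in screened houses". The protocol article answers it in Safety considerations: "We will therefore assess the study children for respiratory disease at each study visit, i.e., twice weekly during the transmission season". Clinical data collection and patient treatments agrees. After setting out the twice-weekly active case detection visits it adds: "Clinical respiratory disease will be determined at the same time". Neither statement carries a condition.

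Clinical evaluations describes what staff do at the visit. Axillary temperature is taken, and at 37.5 °C or above a rapid test "for malaria will be made, and the breathing rate will be checked". The components of the respiratory endpoint "will also be assessed in children deemed to be unwell by the parent or guardian". No respiratory step is described for a child who has no fever and is not reported unwell.

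Study endpoints (Clinical) lists, as the fourth secondary endpoint, "an incidence of respiratory infection, measured as a cough and either a raised age-specific respiratory rate or chest indrawing". Fever and parental opinion are not part of that definition.

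**The concern.** Staff who follow Safety considerations and staff who follow Clinical evaluations would collect different endpoints. Under the first rule, a coughing, fast-breathing child without fever whose parent is not worried is counted. Under the second, that child is not examined.

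This matters because respiratory infection is the only harm named among the objectives and endpoints, and the every-visit assessment is offered as the safeguard against it. Both triggers in Clinical evaluations can depend on the arm. Malaria fever is what improved housing is meant to reduce. The Sample size rationale anticipates a fall in incidence similar to the 65% fall in mosquito entry, and the investigators "consider that a reduction of at least 35 % would not only be of public health importance". Parents know whether their house has been modified, and the Blinding section accepts that full blinding is impossible. A comparison of respiratory rates could therefore partly reflect who was examined. Examinations that were not made cannot be recovered in the analysis.

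**Working it through.** No published figure in the article bears on this point, so there is none to reproduce. The check has two parts: the texts side by side, then how large the fever route could be.

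**1. The texts**

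| Section | Who is assessed | Condition |
|---|---|---|
| Clinical data collection and patient treatments | Study children, at the case detection visits | None |
| Safety considerations | Study children, each twice-weekly visit | None |
| Clinical evaluations, breathing rate | Febrile children | At least 37.5 °C |
| Clinical evaluations, cough with rate or indrawing | Children reported unwell | Parent or guardian deems the child unwell |
| Study endpoints (Clinical) | Definition only | Needs neither fever nor report |

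The two triggers are not equal. Fever leads only to a breathing-rate check; the full endpoint components are attached to the parental trigger.

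**2. Malaria fevers per arm**

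Inputs from the Sample size rationale: 0.0468 and 0.0442 episodes per child-month (2010), 0.0321 and 0.0341 (2011), doubled for active detection; 400 children per arm. Visits run June to November, 6 months in each of two seasons, taken as 26 weeks × 2 = 52 visits per season. I average each pair of rates and count one febrile visit per episode.

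- Rates: 2 × 0.0455 = 0.0910 and 2 × 0.0331 = 0.0662.
- Control arm: 400 × 6 × (0.0910 + 0.0662) ≈ 377 episodes.
- Intervention arm at a 35% reduction: 0.65 × 377 ≈ 245, or about 132 fewer.
- Scheduled visits per arm: 400 × 2 × 52 = 41,600. Malaria fever is present at q = 377/41,600 ≈ 0.9% of control visits, and the 132 averted fevers are about 0.3% of visits.

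**3. Malaria and respiratory illness independent**

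Let s be the chance that a respiratory episode prompts its own check, through its own fever or parental concern. Detection probability = s + (1 − s)q. I assume that a check prompted by malaria fever would record the full endpoint, which is generous to the concern. The article does not give s.

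| s | Detection ratio, intervention/control, 35% reduction | 65% reduction |
|---|---|---|
| 0.05 | 0.949 | 0.904 |
| 0.10 | 0.974 | 0.951 |
| 0.30 | 0.993 | 0.987 |
| 0.50 | 0.997 | 0.994 |
| 1.00 | 1.000 | 1.000 |

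**4. A share f of control detections arises only through malaria illness**

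Apparent rate ratio with no true effect = 1 − f × (malaria reduction). The article does not give f.

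| f | 35% reduction | 65% reduction |
|---|---|---|
| 5% | 0.98 | 0.97 |
| 20% | 0.93 | 0.87 |
| 50% | 0.83 | 0.68 |

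At f = 20%, a true ratio of 1.20 for the remaining episodes would appear as 1.20 × 0.80 + 0.20 × 0.65 = 1.09 at a 35% reduction, or 1.20 × 0.80 + 0.20 × 0.35 = 1.03 at 65%.

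**5. How the two models connect**

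Under independence f = (1 − s)q / [s + (1 − s)q]. A share of 10% then needs s = 9q/(1 + 9q) ≈ 7.5%, and 20% needs s = 4q/(1 + 4q) ≈ 3.5%. Large shares therefore require either that very few respiratory episodes prompt their own check, or that the two illnesses tend to occur together.

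**6. The parental route**

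If parents' readiness to call a child unwell differs by arm, s differs by arm. Because q is small, the detection ratio is then close to the ratio of the two values of s. The article gives no basis for the sign or the size.

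**The case against.** The two rules can be read together. Safety considerations fixes how often children are assessed, and Clinical evaluations gives the procedure: take the temperature, hear whether the parent thinks the child unwell, then examine. That reading is possible, though the article does not state it, and it leaves the same two triggers in place. It removes the contradiction but not the dependence on arm.

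A reader might go further and infer that cutting malaria fevers will necessarily cut detection of respiratory harm, so that a real increase is hidden. One could even put a figure on it: if 10–20% of detections came only through malaria fever, a 35–65% malaria reduction would lose 3.5–13% of detections, and a true rate ratio of 1/(1 − 0.035) = 1.04 to 1/(1 − 0.13) = 1.15 would look like 1.00. The documents do not support this. The 10–20% share has no source, and under independence it needs s of only about 3.5–7.5%, which is hard to accept for episodes of cough with fast breathing or indrawing. Nor is the net direction settled, since parents in modified houses might report more illness or less. Those figures are illustrative at most.

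Other safety capture also counts. Adverse events are collected whether or not they are attributed to housing, serious events reach the safety committee, and suspected pneumonia is referred. The gravest respiratory harm thus has another route to notice, but that route does not feed the stated endpoint.

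Finally, a condensed article may leave visit-form detail to the full protocol. The point here is not missing detail: the article states two different rules.

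**Conclusion.** The point holds as an inconsistency with a possible bias, not as a demonstrated one. Two sections state an unconditional assessment at every visit; the only operational description makes it conditional on fever or parental report; the endpoint requires neither. If the conditional rule governs, ascertainment of the only pre-named harm could differ by arm. The fever route would tend to hide harm, and the parental route could go either way.

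The size runs from nil to material. At a 35% malaria reduction it is under 1% with independent illnesses and s of at least 0.30, and 7% if f is 20%. Both s and f are assumptions that the article does not allow one to fix. The primary malaria endpoint is not affected by this point.

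**What to change.** Reconcile Clinical data collection and patient treatments, Clinical evaluations, Safety considerations and Study endpoints (Clinical) to one ascertainment rule, applied identically in both arms:

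- At every scheduled visit, staff observe every child for cough and ask one standard question about it.
- In every child with cough, they record respiratory rate and chest indrawing, whatever the temperature and whether or not the parent deems the child unwell.
- The number of respiratory assessments is reported by arm, so that a reader can see whether ascertainment was balanced.

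Detection then no longer depends on fever, and the fever-route ratio is 1.00 under both models above. Some dependence on parental report remains, because the answer about cough comes from a parent who knows the allocation; the rule reduces dependence on arm but does not abolish it.

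The cost is one question and an observation at about 83,200 visits (2 × 41,600), plus a breathing count and a look for indrawing in coughing children. Staff are already in the house taking each child's temperature, so no extra visit is needed. Visits will be slightly longer, more so because the article describes respiratory infections as common in the area.
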